## Abstract

**Background:**

Colorectal cancer (CRC) is the third most common cancer worldwide, with 1.9 million new cases in 2020 and a predicted rise to 3.2 million in 2040. Screening programmes are already in place to aid early detection and secondary prevention of CRC, but the rising prevalence means additional approaches are required in both primary and secondary prevention settings. Preventive therapy, whereby natural or synthetic agents are used to prevent, reverse or delay disease development, could be an effective strategy to further reduce cancer risk and potential agents have already been identified in conventional observational studies. However, as such studies are vulnerable to confounding and reverse causation, we aim to evaluate these observed relationships using Mendelian randomization (MR), an alternative causal inference approach which should be less susceptible to these biases.

**Methods and analysis:**

We will use two-sample MR, which uses two independent samples for the exposure and outcome data, to investigate previously reported observational associations of multiple potential preventive agents with CRC risk. We define preventive agents as any synthetic (e.g. approved medication) or natural (e.g. micronutrient, endogenous hormone) molecule used to reduce the risk of cancer. We will first extract potential preventive agents that have been previously linked to CRC risk in observational studies from reviews of the literature. We will then evaluate whether we can develop a genetic instrument for each preventive agent from previously published genome-wide association studies (GWASs) of direct measures of molecular traits (e.g. circulating levels of protein drug targets, blood-based biomarkers of dietary vitamins). The summary statistics from these GWASs, and a large GWAS of CRC, will be used in two-sample MR analyses to investigate the causal effect of putative preventive therapy agents on CRC risk. Sensitivity analyses will be conducted to evaluate the robustness of findings to potential violations of MR assumptions.

## Introduction

Colorectal cancer (CRC) is a major public health issue, being the third most common cancer globally, with an estimated 1.9 million new cases in 2020
^
1–
3
^. A small proportion of cases are attributable to rare, highly penetrant germline mutations; however, the majority of cases are believed to be influenced by a combination of genetic, environmental and lifestyle factors. In many countries cases have been increasing in line with economic growth, given the accompanied elevated exposure to CRC risk factors (e.g. poor diet, lack of exercise, ageing population), and this has led to estimations of new cases reaching 3.2 million in 2040
^
4,
5
^. While in some high-income countries incidence rates have remained relatively stable or even decreased over the last two decades (largely attributable to screening programmes), incidence rates among a younger demographic (i.e., under the age of 50) have increased over this time period
^
6–
8
^.

Prevention is a key strategy for reducing disease burden, and there are a number of approaches that could be used to intervene at different stages of cancer initiation and progression
^
9
^. Primary prevention, where an intervention is deployed in a healthy population (e.g. showing no signs of disease or precursors), can either be employed universally or targeted at higher risk groups (e.g. individuals with Lynch syndrome). Examples of primary prevention strategies include lifestyle interventions promoting smoking cessation and weight loss and pharmacological approaches like aspirin use
^
10
^. Secondary prevention refers to detection of the early stages of, or the precursor to (e.g. polyps for CRC), the disease and intervening before the disease progresses. Screening of CRC is an example of secondary prevention and has been found to reduce cancer incidence and mortality in average-risk groups
^
11
^, through enabling early detection and subsequent removal of pre-cancerous growths
^
4,
7
^. Screening alone is insufficient for reducing disease burden and additional strategies are needed for both primary and secondary prevention, in both the general population and in high-risk groups.

Preventive pharmacological therapy is one strategy that could be employed for CRC prevention, whereby those in the general population or at high risk of CRC would take a therapeutic agent over an extended period of time, consequently reducing their lifetime risk of developing the disease
^
12
^. Preventive therapy agents can be synthetic or natural molecules, such as drugs, dietary micronutrients and endogenous hormones. The biological effect of a preventive agent is often to increase or decrease the concentrations of certain molecules in the blood, which will have downstream effects that can lead to a reduction in cancer development
^
13
^. Conventional observational studies have reported associations between various preventive agents and CRC risk reduction, which has subsequently informed the testing of certain agents in large-scale clinical trials. For example, conventional observational studies suggesting a protective role of aspirin in CRC development
^
14,
15
^ informed design of large-scale randomised controlled trials which have corroborated these findings, supporting aspirin as a preventive agent for CRC
^
16–
18
^. There are risks associated with aspirin use, the most frequently reported relating to gastrointestinal toxicity, and this has been observed with both regular and low-dose use
^
19
^. There is therefore a need to discover other potential preventive agents, with improved safety profiles, that are appropriate for long-term use for the purposes of primary or secondary CRC prevention.

Associations of preventive agents with CRC risk identified from observational evidence are susceptible to biases such as confounding (unmeasured and residual) and reverse causation. Consequently, it is often unclear whether associations identified in these studies represent causal relationships. An alternative epidemiological approach that can be employed to evaluate causal relationships in observational settings is Mendelian randomization (MR), which uses germline genetic variants to instrument exposures to minimise these sources of bias, strengthening causal inference
^
20–
23
^. As alleles of germline genetic variants are randomly assorted at meiosis and fixed from conception, conventional sources of confounding and reverse causation should be minimised.

In order to conduct MR studies, genetic instruments are required that are robustly associated with the exposure of interest. There has been a proliferation of genome-wide association studies (GWASs) that have identified associations between large numbers of traits and germline variants across the genome. These include direct measurements of molecular traits (e.g. levels of protein targets of drugs, circulating dietary biomarkers and endogenous hormones), making it possible to evaluate causal relationships between molecular exposures and outcomes in a two-sample MR framework.

## Aims

The aim of this study is to use two-sample Mendelian randomization to estimate the effect of various previously reported preventive therapies on CRC risk.

## Methods

### Study design

Two-sample MR will be used to investigate the causal relationship between putative preventive therapy agents and risk of CRC. The preventive agents investigated in these analyses will include medications, dietary micronutrients and endogenous hormones. We are prioritising these types of agents as they can be modified through either supplementation (e.g. increasing vitamin levels) or pharmacological perturbation (e.g. inhibiting protein drug targets). For previously reported medications, we will attempt to instrument the target of these medications (e.g. circulating protein targets). For previously reported dietary micronutrients, we will instrument circulating measures of these micronutrients (e.g. blood-based biomarkers for dietary vitamins). For circulating endogenous hormones, these will be instrumented directly. For simplicity we will collectively refer to the different instrument classes (e.g. circulating targets of medications, circulating dietary biomarkers, and circulating endogenous hormones) as molecular traits. Genetic instruments for each molecular trait will be constructed using single nucleotide polymorphisms (SNPs) associated with these molecular traits, obtained from summary statistics of genome-wide association studies (GWASs). We will then extract these SNPs from an independent GWAS of CRC risk to estimate causal effects. The Strengthening the Reporting of Observational Studies in Epidemiology using Mendelian Randomization (STROBE-MR) guidelines (up to and including the methods section)
^
24
^ were used to structure the writing of this protocol.

### Exposure data and instrument selection

A literature search was conducted to identify preventive agents that have previously been linked to reduced CRC risk in conventional observational epidemiological studies. PubMed and EMBASE were searched to identify reviews published from 1
^st^ January 2013 to 7
^th^ November 2023 (
Table 1). After screening, 17 reviews were included and, for each of these, all reported preventive agents were extracted.

**Table 1. T1:** Search terms for literature review of putative preventive agents and CRC risk.

Database	Search terms	No. results
Pubmed	#1 "Colorectal Neoplasms"[MeSH Terms:noexp] OR "Rectal Neoplasms"[MeSH Terms:noexp] OR "bowel cancer"[Title/Abstract]	161,351
	#2 Chemoprevention"[MeSH Terms:noexp] OR "preventive therapy"[Title/Abstract]	10377
	#3 "Review"[Publication Type:noexp] OR "Review"[Title/Abstract]	4,062,927
	#4 "2013/01/01"[Date - Publication] : "2023/11/07"[Date - Publication]	13,813,521
	#5 #1 AND #2 AND #3 AND #4	64
Embase	1 exp colorectal cancer/	392,588
	2 exp colon tumor/	172,044
	3 exp rectum tumor/	78,359
	4 chemoprevention.ab,ti.	14,943
	5 preventive therapy.ab,ti.	5,085
	6 exp "review"/	3,200,578
	7 review.ab,ti.	2,714,988
	8 1 or 2 or 3	441,101
	9 4 or 5	19,979
	10 6 or 7	4,564,148
	11 8 and 9 and 10	915
	12 limit 11 to dc=20130101-20231107	338

*Abbreviations: CRC = colorectal cancer; MeSH = Medical Subject Heading; noexp = no explosion; ab = abstract; ti = title. Search terms used to search PubMed and Embase for reviews of observational studies that had associated preventive therapies with CRC risk, showing number of results returned at each step.*

For all preventive agents identified in the literature search, their effect on CRC risk will be tested. We will attempt to instrument the corresponding molecular trait for each agent. If the preventive agent is a drug, the molecular trait we will be testing will be the biological target of the drug which we will identify using the online databases Open Targets
^
25
^ and DrugBank
^
26
^. There may be challenges in designing instruments for some molecular traits including limited understanding of the mechanism of action of a drug (e.g. metformin) or the absence of genetic variants that are strongly associated with a trait (e.g. reaching genome-wide significance of p<5°10
^-8^). Consequently, these molecular traits will be excluded from subsequent analyses.

For those molecular traits that will be taken forward for further analyses, genetic instruments will be constructed by identifying GWASs that have reported genetic associations with direct measures of molecular traits of interest in populations of European ancestry. These studies, and available instruments, will be searched for using several databases. Firstly, the GWAS catalogue
^
27
^ and the IEU Open GWAS
^
28
^ will be searched, followed by PubMed and medRxiv/bioRxiv for any pre-prints. We will also consult in-house summary genetic association statistics, if necessary, to access restricted and unpublished datasets. Genetic instruments will be constructed by selecting SNPs strongly associated with each trait of interest (p<5°10
^-8^) using summary genetic association data from these studies. For those molecular traits that are protein drug targets or biomarkers, SNPs will be selected that are located in or within proximity to genes that code for that protein (termed
*cis*-variants).
*Cis*-variants are expected to be specific to the target being instrumented which should minimise the likelihood of bias from horizontal pleiotropy. In addition, the use of
*cis*-acting variants that influence protein targets of drugs examined would be expected to enhance instrument strength because protein expression is relatively proximal to germline genetic variants. In the absence of SNPs associated with direct measures of protein targets, we will explore constructing instruments from SNPs associated with downstream biomarker perturbations of drug targets. For those molecular traits that correspond to dietary agents or endogenous hormones, genome-wide significant variants will be selected independent of their genomic position. Of these variants, only those that are independent (r
^2^<0.001) will be included as instrumental variables in the primary analyses. For protein drug targets and biomarkers, we will increase the number of SNPs in our genetic instrument by permitting SNPs to be in weak linkage disequilibrium (e.g. r
^2^<0.10). We will account for this by generating a correlation matrix using a random subset of 10,000 individuals of white British ancestry in the UK Biobank as reference panel and using a generalised IVW method that can account for correlated instruments
^
29
^.

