### Outcome data

Genetic association data for CRC risk will be obtained from a GWAS meta-analysis of colorectal cancer in 78,473 cases and 107,143 controls
^
30
^. This study used data from several studies of individuals of European ancestry, including the Genetics and Epidemiology of Colorectal Cancer Consortium (GECCO), the Colorectal Transdisciplinary Study (CORECT), COloRectal cancer Study of Austria (CORSA) and UK Biobank. This GWAS was adjusted for age, sex and genetic principal components of ancestry (PCs). Details on participants, genotyping and quality control (QC) have been described previously
^
30
^. The summary data from this GWAS is available without UK Biobank data. Where there is sample overlap between the CRC GWAS and the exposure GWAS (i.e. those studies conducted exclusively in UK Biobank) and we have a significant finding from the main analyses after accounting for multiple testing (using a false discovery rate (FDR) correction of <5%), we will conduct a sensitivity analysis using CRC data with UK Biobank excluded. We will also compare the individual studies included in the CRC GWAS with all exposure datasets (i.e. beyond overlap of UK Biobank participants). Where there is a small-to-modest proportion of participant overlap between the studies included in the exposure data and the CRC data, we will quantify this overlap and, for any significant findings, we will repeat analyses using a more stringent F-statistic threshold (e.g.
31) to select genetic instruments. Sample overlap is only an issue if the genetic instruments used are weak
^
32,
33
^, therefore repeating analyses with a more stringent F-statistic threshold should minimise the likelihood of including weak instruments in analyses.

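### SNPs are selected and, as the plan reads, weighted in the same exposure GWAS; this overestimates near-threshold effects, and an F-statistic from that GWAS does not rule out the resulting bias

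*Protocol article*

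**What the plan says.** Under Exposure data and instrument selection: "Genetic instruments will be constructed by selecting SNPs strongly associated with each trait of interest" at p<5×10⁻⁸, "using summary genetic association data from these studies". Under Data harmonisation and Main analyses, the exposure summary statistics are aligned with the CRC data and enter the Wald ratio or IVW. No second exposure sample for the weights, and no correction for selection, is described.

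Under Study design: "We will then extract these SNPs from an independent GWAS of CRC risk to estimate causal effects". The Outcome data section then allows for shared participants and gives the principle "Sample overlap is only an issue if the genetic instruments used are weak". It offers two remedies, both for significant findings only:

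- Where the exposure GWAS was run exclusively in UK Biobank, "we will conduct a sensitivity analysis using CRC data with UK Biobank excluded".
- Where other overlap is small to modest, it is quantified and the analysis is repeated with a stricter F threshold. The example is printed as 31.

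Main analyses takes F>10 as the sign that weak-instrument bias is unlikely.

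**The concern.** A SNP whose true effect lies near the significance threshold tends to pass when sampling error pushes its estimate up. If that estimate is also the weight, the denominator of the Wald ratio is too large on average (winner's curse).

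With separate exposure and outcome samples, this pulls the log OR towards zero. With shared participants, the selected error also appears in the CRC estimate, and the result moves towards the confounded observational association that the study is designed to get away from.

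The Aims section promises estimates of effect, so size matters as well as significance. Traits with one to three SNPs from modest GWASs are most exposed, because one near-threshold SNP can determine the answer. The plan's safeguard is the F-statistic, but that is computed from the data that selected the SNPs.

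**Working it through.** **The plan's own figure.** 78,473 + 107,143 = 185,616, which matches the total in the Figure 1 caption. The article gives no figure for selection bias, and no SNP z-scores, exposure sample sizes or overlap fractions. Everything below therefore rests on stated assumptions: normally distributed SNP estimates and a two-sided selection test.

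**Step 1: what F measures.** In the article's formula for R², the factor 2·MAF(1−MAF) cancels, leaving R² = β²/(β² + N·se²). Then F = R²(N−2)/(1−R²) = (β/se)²(N−2)/N ≈ z². Per SNP, F is the selecting p-value on another scale.

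- p<5×10⁻⁸ means |z|>5.451, so F>29.7.
- F>10 therefore excludes no selected SNP.
- F>31 corresponds to p<2.6×10⁻⁸, almost the same cut.

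**Step 2: one SNP, no overlap.** With c = 5.451 and true z = t, the mean selected z is t + φ(c−t)/[1−Φ(c−t)]; the opposite tail is negligible. At t = 5 this is 6.106, so inflation is 6.106/5 − 1 = 22% and log-OR shrinkage is 1 − 5/6.106 = 18%.

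| True z | Inflation | Log-OR shrinkage | True OR 0.80 reads as |
|---|---|---|---|
| 4.5 | 33% | 25% | 0.846 |
| 5 | 22% | 18% | 0.833 |
| 6 | 8% | 7.5% | 0.813 |
| 7 | 2% | 2% | 0.803 |
| 8 | 0.2% | 0.2% | 0.800 |

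With a cut at F>31 instead, inflation at t = 5 is 24%, so it is not reduced.

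**Step 3: IVW, no overlap.** Simulation with observed z = true z + N(0,1), selection at |z|>5.451, and retained fraction = Σ(z·true z)/Σz².

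| True z distribution | Log-OR shrinkage |
|---|---|
| Normal, SD 1.5 | 31% |
| Normal, SD 2 | 20% |
| Normal, SD 3 | 10% |
| Normal, SD 5 | 4% |
| t with 3 df, scale 1 to 5 | 5% to 1% |

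On the OR scale, 20% shrinkage turns 0.70 into exp(0.8·ln 0.70) = 0.752 and 0.80 into 0.837.

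**Step 4: full overlap, no true effect.** The bias is shown as a share of the confounded association.

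| True z distribution | Mean observed F | Bias share | 1/F |
|---|---|---|---|
| Normal, SD 1.5 | 36 | 30% | 2.8% |
| Normal, SD 2 | 39 | 20% | 2.6% |
| Normal, SD 3 | 47 | 10% | 2.1% |
| Normal, SD 5 | 70 | 4% | 1.4% |

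Under the heavy-tailed distributions it is about 4% to 1%. Partial overlap scales these shares down in proportion. The observed F suggests a much smaller bias than occurs when many selected SNPs lie near the threshold.

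**The case against.** The other side has several good points.

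**The normal model drives part of the result.** If true z is normal with SD s, the retained fraction is s²/(1+s²) at any threshold on observed z (for s = 2, 4/5 = 0.80). A reader might infer that no observed-F cut can help. That does not follow. Under t effects with 3 df and scale 1, the retained log OR rises from 95% at F>29.7 to 97% at F>50 and 99% at F>100. Under Laplace effects with scale 1 it rises from 85% to 88% and 91%. A much higher cut may help, depending on a distribution that the article does not give. The printed 31 does not.

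**The 31 is doubtful.** The next citations in that paragraph are 32 and 33, and the Power section cites 31, so the number may be a citation mark. It is in any case only an example.

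**Overlap is partly handled.** The re-run without UK Biobank removes that shared error for significant findings from exposures measured exclusively there. It does not remove the shrinkage towards the null. The full-overlap figures are a limit: the stricter-F remedy is for small-to-modest overlap.

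**Truly strong SNPs are safe.** Selection bias is about 2% at a true z of 7 and fades above that, which is close to what the overlap sentence means.

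**Detail may sit elsewhere.** A condensed article can leave sensitivity analyses to a fuller plan, and this one does not forbid separate weights. But it does state the overlap principle and the F remedy, and those can be judged as written.

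**Conclusion.** The point holds, with its size left as a range. Selecting and weighting in one GWAS overestimates the effects of near-threshold SNPs. Neither F>10 nor the printed F>31, computed in that GWAS, detects or removes this. Single-SNP log-OR shrinkage runs from about 25% at a true z of 4.5 to about 0% from 8. IVW shrinkage runs from about 1% to 31% over the distributions tried, which were chosen only to show a range.

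Two stronger readings are not supported:

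- A reader might conclude that ORs are biased by up to about 20%. That figure is log-OR shrinkage under one assumed distribution. It is not a maximum, and on the OR scale it changes 0.70 by about 7% (0.752/0.70 = 1.074). Nothing in the article fixes the size for any trait in Table 2.
- A reader might conclude that the overlap premise is simply false. Overlap does matter mainly for SNPs that are truly weaker. What fails is judging strength by F from the selecting sample.

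Without overlap the bias costs effect size but produces no false positives. With overlap it can favour the confounded association, in proportion to the overlapping fraction.

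**What to change.** 1. In Outcome data, replace the absolute sentence on overlap with one saying that overlap bias can also arise from selecting SNPs in the overlapping sample, and that the F observed there does not rule it out. Also make clear whether 31 is a threshold or a citation.
2. For each FDR-significant finding, add one sensitivity estimate, with R² and F recomputed. Use either a selection-corrected estimate (conditional likelihood or equivalent shrinkage of the SNP-exposure effects) or, where a suitable second exposure GWAS exists, weights from it. That GWAS must share no participants with the selecting GWAS or the CRC GWAS.

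The primary analysis can stay as it is. Requiring split-sample weights throughout would cost precision and is open to debate. The cost of the fix is some wording, a little extra analysis of summary data, and wider intervals for the sensitivity estimate. According to Study status, instruments are still being identified, so the change can be made now.

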### Sensitivity analyses

For instrumental variable sets that use more than one genetic instrument, the analyses will be iteratively repeated, each time leaving out one SNP to test if there is a particular SNP that is driving results, which could be due to the outlying SNP being the only valid instrument or due to this SNP being horizontally pleiotropic.

We will apply “pleiotropy-robust” models as sensitivity analyses when sufficient independent genetic instruments are available (e.g. ≥ 10), given low statistical power of these models. These models include the weighted median
^
38
^, weighted mode
^
39
^ and MR Egger
^
40
^ regression and effect estimates from these methods can be compared to the IVW estimate obtained in initial analyses to evaluate if observed effects are possibly driven by horizontal pleiotropy. The weighted median can provide an unbiased causal estimate even when some of the genetic instruments used are invalid, the weighted mode effect estimate is more robust to horizontal pleiotropy, and the MR-Egger regression intercept can provide an indication of directional (i.e. unbalanced) pleiotropy. Whilst these sensitivity analyses relax certain assumptions of the IVW method, these models introduce new assumptions, so it is therefore important to use all three methods for comparison. If a consistent effect is observed across these three methods and the IVW estimate obtained from the main analyses, it is less likely that this finding is driven by violations of MR assumptions. To support these findings we will also use MR-PRESSO
^
41
^ to detect, and correct for, horizontal pleiotropy. This method assumes the majority of SNPs used as instruments are valid. 

For any exposures found to be associated with CRC risk, after applying an FDR correction, Steiger filtering will be used to explore the causal direction of SNP effects
^
42
^. The steiger_filtering function in the TwoSampleMR package will be used to evaluate if findings are driven by reverse causation, whereby the SNP used to instrument a molecular trait has an effect on CRC which in turn impacts variation in the molecular trait.

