## Study status

At the time of submission of this protocol for publication, preventive agents have been identified from the literature and we have identified the corresponding molecular trait for each agent. We have determined which molecular traits are instrumentable and, for those that are (
Table 2), we have begun to identify genetic instruments.

**Table 2. T2:** Preventive agents identified in the literature to be associated with CRC risk reduction.

Preventive agent	Molecular trait
Dietary long-chain omega-3 polyunsaturated fatty acids	Circulating long-chain omega-3 polyunsaturated fatty acids
Dietary long-chain omega-6 polyunsaturated fatty acids	Circulating long-chain omega-6 polyunsaturated fatty acids
Dietary salicylic acid	Plasma salicylic acid levels
Dietary calcium	Serum calcium levels
Dietary vitamin D	Serum 25 hydroxyvitamin D
Dietary folate levels	Serum folate levels
Dietary selenium	Circulating selenium levels
Dietary vitamin A	Serum retinol levels
Dietary vitamin C	Plasma vitamin C levels
Dietary vitamin E	Circulating alpha-tocopherol levels
Dietary β carotene	Circulating β carotene levels
Dietary magnesium	Serum magnesium levels
Statins	Circulating LDL cholesterol levels (due to HMG-CoA reductase inhibition)
Guselkumab	Plasma IL23 protein levels
Antihypertensives	Serum ACE levels
	SBP (due to NCC inhibition)
	SBP (due to ADRB1 inhibition)
Testosterone	Circulating testosterone levels
Estradiol	Serum estradiol levels
Sex hormone binding globulin	Serum SHBG levels
Progesterone/17- hydroxyprogesterone	Circulating progesterone/17- hydroxyprogesterone levels

Abbreviations: CRC = colorectal cancer; LDL = low-density lipoprotein; HMG-CoA = 3-hydroxy-3-methylglutaryl coenzyme A; IL23 = interleukin 23; ACE = angiotensin-converting enzyme; SBP = systolic blood pressure; NCC = sodium chloride cotransporter; ADRB1 = β1 adrenoceptor; SHBG = sex hormone binding globulin. Preventive agents identified in the literature that had a corresponding molecular trait that was deemed instrumentable. These agents included dietary micronutrients, drugs and endogenous hormones. For each drug, the biological target of the drug was identified as it’s molecular trait, (e.g. the levels of the protein that the drug targets). For dietary micronutrients and endogenous hormones, molecular traits were identified that correspond to the agent (e.g. blood-based biomarkers for vitamin levels).

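### The cis rule does not say which IL-23 gene may instrument guselkumab, so the target specificity expected of cis-variants is not secured for this trait

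*Protocol article*

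**What the plan says.** All references are to the protocol article.

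- **Target definition** (Exposure data and instrument selection), for medications: "the molecular trait we will be testing will be the biological target of the drug which we will identify using the online databases Open Targets". The second source named is DrugBank.
- **SNP selection** (same section): for protein drug targets and biomarkers, "SNPs will be selected that are located in or within proximity to genes that code for that protein". No gene, subunit or window is given for any target.
- **Reason for the rule** (same section): cis-"variants are expected to be specific to the target being instrumented which should minimise the likelihood of bias from horizontal pleiotropy".
- **Guselkumab** (Study status, Table 2): the trait is "Plasma IL23 protein levels". The statin row and two of the three antihypertensive entries name the inhibited protein (HMG-CoA reductase, NCC, ADRB1), which points to a locus. The guselkumab row names nothing narrower than IL23.
- **Progress** (Study status): the trait for each agent has been identified and instrumentability has been judged. For the SNPs themselves, "we have begun to identify genetic instruments".

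**The concern.** A cis rule protects against horizontal pleiotropy only if the gene in question acts through the drug's target and nothing else. This usually holds when one gene codes for one protein. It can fail when a target is built from the products of two genes and one of those products also forms part of another protein.

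On the assumption about IL-23 set out in the working, IL12B is such a gene. A variant there would meet the written cis definition for IL-23 and could also alter IL-12, which guselkumab does not target. An association of that variant with colorectal cancer could arise through either cytokine, yet it would be reported in the guselkumab row. The study aims to say which agents are worth pursuing for prevention, so the risk is credit, or lack of it, given to the wrong target.

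**Working it through.** **1. Inputs from the documents.** The selection rule, its rationale and the Table 2 entry are as set out above. The plan contains no figure on this point, so there is nothing to reproduce. No stated sample size, significance level or power value depends on it.

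**2. Assumption from outside the documents.** IL-23 consists of p19 (IL23A) and p40 (IL12B), p40 is also part of IL-12, and guselkumab binds p19. The documents mention neither IL-12 nor the subunits. If this assumption were wrong, the point would fall.

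**3. Rule applied to the trait.** The rule pairs a plural (genes) with a single protein, and the trait is IL23 as a whole. On the assumption, both IL23A and IL12B code for part of it, so SNPs near either are eligible. Nothing excludes IL12B. Equally, nothing says that IL12B will be used.

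**4. Would a planned safeguard show it?**

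| Planned step | Would it detect an IL-12 path? |
|---|---|
| Leave-one-out, for any multi-SNP instrument | Possibly, if both genes contribute. Less clearly if several SNPs lie at one gene, since one is dropped at a time. No, if all lie at IL12B. |
| Multiplicative random-effects IVW | Widens the interval if the two genes disagree. With about three SNPs or fewer the plan uses fixed effects, which does not. |
| Weighted median, weighted mode, MR-Egger | Planned at about 10 or more independent SNPs, which a cis instrument may not supply. For protein targets "we will increase the number of SNPs in our genetic instrument by permitting SNPs to be in weak linkage disequilibrium", which adds correlated SNPs, not independent ones. |
| Multivariable MR | Only for FDR-significant findings with overlapping instruments. IL-12 is not a Table 2 trait. |
| Colocalisation | No. It tests whether a causal variant is shared, not which protein that variant acts through. |

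**5. Illustration of size, with assumed inputs only.** Let θ be the log odds ratio for IL-23, w the share of IVW weight carried by IL12B SNPs, and α their off-target log odds ratio per SD of the instrumented trait. Then

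estimate = θ + w × α.

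The documents give neither w nor α. Suppose IL-23 has no effect (θ = 0), and take off-target odds ratios of 0.90 and 0.80, two of the three effect sizes in the plan's power figure. The estimated odds ratio is exp(w × ln OR):

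| w | off-target OR 0.90 | off-target OR 0.80 |
|---|---|---|
| 0.10 | 0.990 | 0.978 |
| 0.25 | 0.974 | 0.946 |
| 0.50 | 0.949 | 0.894 |
| 1.00 | 0.900 | 0.800 |

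The sign could also be the reverse. With a true IL-23 odds ratio of 0.90 (θ = −0.105) and α = +0.105, chosen to be equal and opposite, w = 0.5 gives −0.105 + 0.053, about −0.053 before rounding, an odds ratio of about 0.95. With w = 1 the estimate is 0, an odds ratio of 1.00.

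So the distortion runs from nothing (w = 0 or α = 0) to the full off-target effect (w = 1), in either direction.

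**The case against.** The strongest reply is that the plan has not yet gone wrong. The cis sentence covers all protein targets, so its plural may be loose drafting and not a decision to pool subunit genes. The plan identifies each drug's target from two databases before selecting SNPs, and that step could point to one gene. The instruments are still being assembled, and qualifying SNPs may turn out to lie at one locus only. Leave-one-out has no 10-SNP minimum and is intended partly to find a pleiotropic SNP. The subunit facts are not in the documents, and an article may leave gene lists to a fuller document.

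Most of this stands as a limit on the point. A reader might infer that the guselkumab instrument is non-specific, or that its estimate will be biased. The documents do not support that, because no SNP has been fixed and neither the weight at IL12B nor any IL-12 effect is given.

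The reply does not remove the gap. Study status reports trait identification as done, and its recorded result is whole IL23, with no later narrowing step described. Leave-one-out helps only when both genes contribute. The point is also not a request for a gene list in general. It concerns one named trait for which the rule as written, on the stated assumption, admits variants that defeat the reason given for the rule.

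**Conclusion.** The point holds in a limited form. The rule does not settle which coding gene counts as cis when a target is made from more than one, and Table 2 does not settle it for IL23. Given the assumed p19/p40 structure and p19 binding, IL12B variants are eligible, and the expected specificity is not secured for guselkumab. Colocalisation and multivariable MR as planned would not show the problem.

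Neither the size nor the direction of any bias can be established. The odds ratios in the working are illustrations and not estimates. The stronger conclusion, that the instrument is already invalid, should not be drawn. One of 21 molecular traits in Table 2 is affected. This is a cheap improvement, best made now while instruments are still being chosen.

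**What to change.** In Exposure data and instrument selection, and in the guselkumab row of Table 2:

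1. Limit the guselkumab instrument to variants in or near IL23A, and state the window.
2. If none reaches p<5×10⁻⁸ for the protein, use the plan's downstream-biomarker fallback only with variants at that drug-target gene.
3. If that also fails, exclude the trait under the plan's existing rule for traits that cannot be instrumented.
4. If IL12B variants are analysed, report them as a separate IL-12/IL-23 p40 trait and draw no conclusion about guselkumab from them.

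The cost is about one line in the table and one in the rule. The downside is that the guselkumab trait may be left with few SNPs or none, and so drop out. A separate p40 trait would add one test to those covered by the FDR correction.
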